## Abstract

**Background:**

In the ‘Tailored Implementation for Chronic Diseases (TICD)’ project, five tailored implementation programs to improve healthcare delivery in different chronic conditions have been developed. These programs will be evaluated in distinct cluster-randomized controlled trials. This protocol describes the process evaluation across these trials, which aims to identify determinants of change in chronic illness care, to examine the validity of the tailoring methods that were applied, and to analyze the association of implementation activities and the effectiveness of the program.

**Methods:**

A multilevel approach was used to develop five tailored implementation interventions. In order to guide the process evaluation in five distinct trials, the study protocols for the cluster randomized trials and the related process evaluations were developed simultaneously and iteratively.

**Results:**

The process evaluation comprises three main components: a structured survey with health professionals in the trials, semi-structured interviews with a purposeful sample of this study population, and standardized documentation of organizational practice characteristics. Norway will only conduct the qualitative part of the analysis because the survey and documentation of practice characteristics are considered to be not feasible. The evaluation is guided by ‘logic models’ of the implementation programs: frameworks that specify the linkages between the strategies used, the determinants addressed by tailoring, and the anticipated outcomes. Standardization of measures across trials is sought to facilitate analysis of aggregated data from the trials.

**Conclusions:**

This process evaluation will need to find a balance between standardization of methods across trials and the tailoring of measures to the specificities of each trial.

## Background

‘Tailored interventions’ are commonly defined as interventions that are designed to address previously identified determinants of practice (also called ‘barriers to and enablers of change’) [1]. A range of different methods has been used for tailoring, but there is little insight into how tailoring is best conducted in order to optimize the effectiveness of interventions [2]. The overall aim of the ‘Tailored Implementation for Chronic Disease (TICD)’ project is to provide insight into methods for tailoring implementation programs to determinants of implementation of evidence-based healthcare for patients with chronic illness [3]. Research teams from five European countries participate in the TICD project, each focusing on a specific clinical condition: chronic obstructive pulmonary disease (COPD) in Poland, obesity in the United Kingdom, cardiovascular diseases in The Netherlands, depression in the elderly in Norway, and multimorbidity in Germany.

Addressing the identified determinants of practice in chronic illness care requires complex interventions, meaning interventions that have multiple components which interact with each other. In the TICD project, five tailored implementation interventions were developed, each of which will be evaluated in a cluster-randomized trial [4-8].

A frequent criticism of evaluations of complex interventions is their lack of detail in both description and analysis on what components of the intervention and which contextual factors contributed to the (lack of) effectiveness [9]. We planned process evaluations in the TICD trials aiming to address this by exploring which factors are associated with change [10,11]. This knowledge is essential for understanding the potential causal mechanisms underlying the effectiveness of interventions as well as for ensuring generalizability of intervention effectiveness across populations and settings [12]. At the same time, this will provide insight into the validity of tailoring methods that were applied in earlier phases of the TICD project.

A factor of specific interest is the degree to which the offered interventions were applied as planned by the participants (depending on the context this has been labeled ‘fidelity’ or ‘integrity’ of the intervention [13]). This knowledge is important to draw valid conclusions about intervention effectiveness and the underlying change mechanisms. Potentially useful interventions may appear ineffective due to low or mistaken application as compared to the original plan [13]. On the other hand, low fidelity or integrity may reflect the adaptation of interventions in the delivery phase to optimize their effectiveness.

Here, we aim to describe the planned process evaluations that are intended to answer the following questions:

1. To what extent did the practitioners or patients use the various components of the planned intervention programs?

2. What is the validity of the methods used to tailor the implementation program to determinants of practice?

3. Which factors are associated with effective implementation of evidence-based practice in chronic illness care, after use of a tailored implementation program?

4. How consistent are the findings regarding the previous questions across the five trials?

## Methods

### Tailoring concept within the Tailored Implementation for Chronic Diseases project

The overall approach in the TICD project has been described elsewhere [3] and is summarized here. As depicted in Figure 1, the tailoring process in the TICD project is divided into five phases. In the first phase, a checklist of determinants of practice was developed to support the design and evaluation of implementation strategies [14]. Additionally, each team identified evidence-based recommendations and relevant literature for the targeted conditions. In the second phase, determinants of practice were identified in all countries. A combination of methods was used for this purpose: brainstorming and group interviews with health professionals, individual interviews with health professionals and patients, and a written survey for health professionals. The identified determinants were evaluated according to their plausible importance and the degree to which they could be addressed in an intervention study. In the third phase, different methods (open group interviews and structured group work with health care professionals, researchers and other stakeholders) were used to identify strategies to overcome the identified barriers for the specific recommendations. In the fourth phase, the identified strategies were prioritized on the basis of the criteria ‘feasibility’ and ‘assumed impact’. These four phases have been conducted in all countries, and based on this prior work, five tailored implementation interventions were elaborated, each of which will be evaluated in a cluster randomized controlled trial [4-8]. In the delivery phase, implementation interventions may be adapted by adjusting interventions to individual or practice-related factors.

**Figure 1 F1:**
[figure not shown]
Tailoring process in Tailored Implementation for Chronic Diseases (TICD) projects.

### Development of a process evaluation protocol

The study protocols for the cluster randomized trials and the related process evaluations were developed simultaneously and iteratively, using email and telephone conversations among research teams to provide feedback and discuss controversial aspects. The project coordinator monitored and protected the coherence of the protocols and their fit with the overall aims of the TICD project.

## Results

### Logic models

To facilitate the measurement and analysis all TICD implementation programs will be operationalized into a ‘logic’ (or ‘explanatory’) model comprising an anticipated model of change mechanisms based on the results of the tailoring process of each implementation intervention. These models describe the hypothesized linkages between determinants, interventions, and outcomes (Figure 2).

**Figure 2 F2:**
[figure not shown]
Logic model of Tailored Implementation for Chronic Diseases (TICD) implementation interventions.

### Setting/target groups of the process evaluation

The intervention programs in the TICD project are situated in primary care settings and target physicians, nurses, and patients and their relatives. The study population in the process evaluation comprises the healthcare professionals of the intervention group, however implementation activities (whether planned or not) will be documented in the control arms as well.

### Data collection

The process evaluation has three main items: a survey with two components (A1 and A2), an interview study (B), and documentation of practice characteristics (C).

#### A1 - Survey on perceived change of determinants of practice

We will perform written surveys in participating health professionals at the primary follow-up measurement in the trials (except in the Norwegian trial, where this survey is considered to be not feasible). As the content of the studies differs, we have developed a frame of the questionnaire that needs to be adapted to the relevant content (Table 1). The questionnaire lists the determinants of practice, which were identified and prioritized in an earlier phase of the TICD project (regardless of whether they are addressed by the implementation program), with the question to assess whether the program successfully targeted them. A free text field is used to identify other determinants that are lacking from this list and are perceived to have major impact.

**Table 1 T1:** Scheme of a questionnaire to examine the validity of the methods used for tailoring (A1)

**Standardized list of determinants (result of phase 2). Please list all determinants, no matter if they are intended to be addressed by the implementation program or not**	**Was this determinant in your opinion clearly addressed by the implementation program?**		
	**Yes**	**Partly**	**No**
Determinant 1	□	□	□
Determinant 2	□	□	□
…			
Free text field: Can you think of other factors, not yet listed above?			

#### A2 - Survey to document implementation activities

The survey of participants also contains questions on the actual implementation activities. We intend to record the extent to which the target group used the offered interventions and adaptions on it in the delivery phase of the implementation programs. Table 2 shows the frame of the questionnaire used in all studies to document implementation activities. The design of the questionnaire is based on a published framework [15], which distinguishes four aspects of intervention fidelity:

1. Content - Was the content of the intervention delivered as planned?

2. Duration - Was the intervention fully implemented across the intended time period?

3. Frequency - Was the intervention conducted as frequent as planned?

4. Coverage - Was the intervention applied to all individuals in the targeted group?

**Table 2 T2:** Questionnaire to document implementation activities (A2)

	**Yes**	**Partly**	**No**
**Intervention component 1:** Please describe the intervention component in sufficient detail (specify content, duration, frequency, coverage if applicable)			
Did you use this item as described in terms of duration? (if applicable)	□	□	□
Did you use this item as described in terms of frequency? (if applicable)	□	□	□
Did you use this item as described in terms of coverage? (if applicable)	□	□	□
Did you find this item helpful for the implementation of the recommendation/to reach the targets?	□	□	□
Did you adapt the content or format of this item in any way? If yes, please specify below!	□	□	□
**Intervention component 2:** Please describe the intervention component in sufficient detail (specify content, duration, frequency, coverage if applicable)			
…	□	□	□
Comments:			
Free text field: Can you think of other intervention components which might have been more helpful in order to improve the implementation of the recommendations/to reach the targets?			

For each implementation program the core components will be specified. For each core component, content, duration, frequency and coverage will be recorded in a structured way (Table 2). The content of the items will be specific for the different trials. A free text field is added to identify strategies that have been missed in the tailoring process so far, allowing the evaluation of the methods used for tailoring.

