### Data analysis

We will use the following analytical approach to answer the research questions addressed by this process evaluation:

1. Research question 1 - To what extent did the practitioners or patients use the various components of the planned intervention programs? and

2. Research question 2 - What is the validity of the methods used to tailor the implementation program to determinants of practice?In order to answer these questions a descriptive analysis of qualitative and quantitative data will be done separately in each country. The descriptive analysis of questionnaires will result in tables with frequency distributions. The qualitative interviews will be transcribed verbatim in the original languages. An iterative thematic analysis will be done, involving two or more researchers in order to identify key themes relevant for implementation.

3. Research question 3 - Which factors are associated with implementation of evidence-based practice in chronic illness care, after use of a tailored implementation program?

To answer this research question a summary outcome measure will be constructed in each trial, expressing professional performance by aggregating items reflecting implementation of evidence-based recommendations. This outcome will be standardized and taken as dependent variable in a regression analysis approach. The independent variables in this model will be a limited number of questionnaire items (to reduce chance capitalization), selected according to hypothesis informed by relevant key themes of the interviews. A special focus will be given to the association between professional performance and the questionnaire items concerning the application and adaption of the implementation program by the target group.

4. Research question 4 - How consistent are the findings across the trials?

A meta-analysis of quantitative and a meta-ethnography of qualitative data from all five studies will be conducted.

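### Table 2 asks about adaptation only for content or format, so the structured data cannot tell a deliberate change in duration, frequency or coverage from lapsed or mistaken application

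*Protocol article*

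**What the plan says.** The Background gives low fidelity two possible meanings. One is that a useful intervention was applied too little or wrongly. The other is that "low fidelity or integrity may reflect the adaptation of interventions in the delivery phase to optimize their effectiveness". The section on the tailoring concept permits such changes: "In the delivery phase, implementation interventions may be adapted by adjusting interventions to individual or practice-related factors".

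The section on survey A2 sets the aim accordingly: "We intend to record the extent to which the target group used the offered interventions and adaptions on it in the delivery phase". It takes content, duration, frequency and coverage as the four aspects of fidelity. It presents Table 2 as the common questionnaire frame, with item content made specific to each trial.

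For each component, Table 2 has one row each for duration, frequency and coverage, all built the same way. The frequency row begins "Did you use this item as described in terms of frequency? (if applicable". The options are *Yes*, *Partly* and *No*, and no reason is requested. A row on helpfulness follows, then the one adaptation row: "Did you adapt the content or format of this item in any way? If yes, please specify below". A general comments field and a free-text question on other useful components close the table.

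Under Data analysis, research questions 1 and 2 are answered descriptively in each country, with frequency tables for the questionnaires alongside the qualitative data. Research question 3 regresses a standardized performance outcome on a small set of questionnaire items, with special attention to "questionnaire items concerning the application and adaption of the implementation program by the target group".

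**The concern.** The article recognises that a departure from the described use may be a lapse or an intended adjustment, and it says A2 will record adaptations. The instrument asks about adaptation for only part of what can be adapted. A practice that chooses to offer a component to selected patients, or to run it less often because that suits its patients, can give the same answers as a practice that let the component slip.

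Two analyses are exposed. For research question 1, the frequency of *Partly* and *No* answers on the application rows would pool both kinds of practice. For research question 3, an application row used as a predictor would mix behaviours that the Background asks the reader to keep apart, and its coefficient would be hard to interpret. Predictors identified there are carried into the pooled analysis under research question 4, so the ambiguity could travel across trials.

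The omission lies in data collection. An analysis plan can fix coding later, but it cannot recover a distinction that the questionnaire never asked for.

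**Working it through.** No arithmetic applies. The article defines no fidelity score and gives no figure that bears on this point. The check sets the Table 2 rows against the four aspects of fidelity and then follows two hypothetical practices through the form.

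**Step 1. Rows available for each aspect.**

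| Aspect | Row on use as described | Named in the adaptation row |
|---|---|---|
| Content | no | yes |
| Duration | yes | no |
| Frequency | yes | no |
| Coverage | yes | no |

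Three of the four aspects have a use row without a matching adaptation row. Content is the reverse. No aspect has both, so for none can a departure be paired with a structured statement that it was intended.

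**Step 2. What adaptation is permitted.** The tailoring section allows adjustment to the individual or the practice and names no aspect as excluded. Changes in duration, frequency and coverage are therefore within what the programmes allow, and A2's stated aim takes in adaptations generally.

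**Step 3. Two practices, same component.** Practice A deliberately restricts the component to some of its patients. Practice B meant to offer it to all and did not keep it up. Neither changed content or format.

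| Row | Practice A | Practice B |
|---|---|---|
| Coverage as described | *Partly* | *Partly* |
| Adapted content or format | *No* | *No* |
| Adaptation row naming coverage (proposed) | *Yes*, coverage, with reason | *No* |

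On the present form the two records are identical. On the reworded form they differ. The same comparison works for duration and frequency.

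**Step 4. Other sources in the article.** The request to specify is triggered only by a positive answer on content or format. The comments field does not prompt for reasons. The interview format in section B asks which components helped and why, or why not, and about outside factors. It has no question on adaptation, and it reaches a purposive sample, so it cannot classify the survey answers of professionals who were not interviewed.

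**Step 5. Scope.** The survey is not done in the Norwegian trial, so the point concerns the four trials that use it.

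**The case against.** The case against has several parts.

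- **The article does not treat departures as failure.** A reader might infer that Table 2 scores any departure as lower fidelity, and that permitted adaptation will be counted as failed implementation or reported as non-use. The document does not support that. It defines no score, cut-off or failure category, it plans frequency tables read alongside interviews, and the Background expressly allows that low fidelity may be adaptation. A *Partly* on coverage truthfully reports partial use as described, whatever the motive. This objection stands in full and limits the point to a missing distinction.
- **The regression harm is not shown.** A reader might also infer that the two behaviours pull performance in opposite directions and cancel out. The Background says adaptation may aim at better effectiveness, not that it achieves it. Nor does the article commit to entering these particular rows as predictors. This stands too: confusion is possible, but cancellation is not established.
- **Respondents may use other routes.** Some may read format to include scheduling, some may write comments, and the interview format can be revised after 5 to 10 interviews. This stands in part. Coverage is hard to read as format, and Table 2 itself treats duration, frequency and coverage as rows of their own. None of these routes yields a structured answer from every respondent.
- **Table 2 is a frame, and the trial questionnaires are not shown.** This is true, and a trial team could add the missing wording. But the frame is the shared instrument on which pooling relies, so the wording belongs there.

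**Conclusion.** The point holds as a gap in the instrument. For duration, frequency and coverage, Table 2 gives no structured means of separating deliberate adaptation from lapsed or mistaken application, although the article permits such adaptation and sets A2 the task of recording it. The frequency tables for research question 1, and any model for research question 3 that uses these rows, may confuse the two.

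The size can be given only as scope: three of four fidelity aspects, for every component to which the rows apply, in the four trials that run the survey. The share of *Partly* or *No* answers that would be deliberate is unknown, and the document offers no basis for a figure. The conclusion assumes that respondents take the adaptation row as worded and that the trial questionnaires keep the rows of the frame.

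The change is worth making because it costs little and cannot be made after the survey. It does not call the trials' effectiveness results into question.

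**What to change.** Reword the adaptation row in the Table 2 frame along these lines: *Did you deliberately adapt the content, format, duration, frequency or target group (coverage) of this item? If yes, please specify which and why.*

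For research questions 1 and 3, read *Partly* and *No* on the application rows jointly with this row, and report deliberate adaptation separately from other departures. The answer on which aspect was changed must be coded by aspect. Otherwise a practice that adapted the content and let the frequency lapse would be misclassified.

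The cost is a slightly longer item for each component and some coding of the specified text. The reasons are self-reported and may lean towards *deliberate*, so the separation will be imperfect. A reason tick-box after each application row would give more detail, but it means up to three extra questions per component and is optional. The article describes the trial as still in planning and the survey takes place at the primary follow-up, so the rewording can be done in time.

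### Table 2 has no row for content used as planned and none for whether a component was used at all, although the A2 survey is meant to record both

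*Protocol article*

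**What the plan says.** The opening of section A2 sets two aims: "We intend to record the extent to which the target group used the offered interventions and adaptions on it in the delivery phase". The section then lists four aspects of fidelity from a published framework, the first being "Content - Was the content of the intervention delivered as planned". After the table it states that "For each core component, content, duration, frequency and coverage will be recorded in a structured way (Table 2".

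Table 2 is the common frame for the studies, with components and wording filled in by each trial. Under a heading that describes the component, it has five rows answered Yes, Partly or No:

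1. "Did you use this item as described in terms of duration? (if applicable"
2. "Did you use this item as described in terms of frequency? (if applicable"
3. the same question for coverage
4. whether the item was helpful
5. "Did you adapt the content or format of this item in any way", with a request to specify if yes

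Under Data analysis, question 1 (extent of use) is answered with frequency tables and interview material. The regression for question 3 gives special focus to "the questionnaire items concerning the application and adaption of the implementation program". The Background warns that low application can hide a useful intervention, but also that "low fidelity or integrity may reflect the adaptation of interventions in the delivery phase to optimize their effectiveness".

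**The concern.** The text describing the instrument and the instrument itself disagree. Content is named first among the four aspects and is said to be recorded in structured form, yet it has no row of its own. Extent of use is the first purpose of the survey and the subject of question 1, yet no row asks about use as such.

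These rows supply the frequency tables for question 1 and the special-focus predictors for question 3. The predictors identified there are then carried into the cross-trial meta-analysis. If the answers do not separate someone who ignored a component from someone who used it differently, the tables and regression coefficients mix two groups that the Background treats as different in meaning. A question that was not asked at follow-up is hard to reconstruct later.

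**Working it through.** The plan gives no figure to reproduce. The check sets the stated aspects beside the printed rows and then asks what each answer can mean.

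**Step 1: aspects against rows.**

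| Stated aspect | Row on use as described |
|---|---|
| Content | none |
| Duration | yes |
| Frequency | yes |
| Coverage | yes |

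Three of four match. In the component heading, content is part of the description given to the respondent, not something the respondent answers.

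**Step 2: what the adaptation row gives for content.** A Yes may concern content or format, and only the free text can separate them. A No is true for a user who changed nothing, and equally true for someone who never used the component.

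**Step 3: what a No on a use row means.** A No on duration, frequency or coverage is given by a non-user and by a user who departed from the plan on that aspect. A Yes on any applicable use row does show use.

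**Step 4: counting the ambiguous answer patterns.** Assumptions: Partly is left out; a non-user answers No to every applicable row; a user who changes content or format reports it; helpfulness is ignored because it is not a fidelity item. If *k* of the three use rows apply to a component, the use rows and the adaptation row together give 2^(k+1) patterns. Two kinds are ambiguous:

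- All use rows No and not adapted: 1 pattern, shared by the non-user and by a user who kept the content but departed on every applicable use row.
- Adapted: 2^k patterns, each mixing changed content with changed format only.

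For k = 3 this gives 1 + 8 = 9 of 16. For k = 0 it gives 1 + 1 = 2 of 2, and there the first pattern is shared by the non-user and a fully faithful user. If the free text always says whether content or format was changed, the adapted patterns resolve and 1 of 16 (k = 3) or 1 of 2 (k = 0) remains. These are counts of patterns, not of respondents.

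**Step 5: effect on the planned analyses.** A frequency table of a single row uses no joint pattern, so every non-user who answers No is counted with those who used the component differently. In the regression, if the adaptation item enters as printed and non-users answer No, the not-adapted group contains both non-users and users who changed nothing.

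**The case against.** Several counter-arguments have force.

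- **Content is not left unmeasured.** A reader might infer that it is. For users, however, the adaptation row is largely the reverse of delivery as planned, and the request to specify can show what was changed. This stands. Content is captured indirectly, and a part left out but not regarded as an adaptation could be missed.
- **Non-users are not scored as faithful.** This reading is tempting because a No on adaptation looks like fidelity. The article gives no scoring rule, and a non-user might leave the row blank or use the comments line. What can be said is that this row does not tell a non-user from a user who changed nothing.
- **Non-use is not invisible.** Where use rows apply, a non-user would probably answer No to them. This stands, but that No is shared with use other than as described.
- **The Background distinction survives in part.** Fidelity, adaptation and helpfulness are separate rows, so a faithful user and an adapter can usually be told apart. The gap mainly concerns non-users.
- **Table 2 is a frame in a condensed article.** The fielded forms are not shown and may contain a filter question. But the frame is the shared instrument, and the text says this table already covers content. Local additions would not restore a common measure.
- **Interviews add information.** They do, but for a purposive sample only, and the listed questions do not go through components one by one.

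**Conclusion.** The point holds as a mismatch between the A2 text and its own table, and as a partial confounding of non-use with use other than as described. One of the four stated aspects lacks a direct row, and there is no row for use itself. The mismatch is read directly from the article. The pattern counts rest on the assumptions stated with them, chiefly that non-users answer No rather than leaving rows blank.

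The documents give no rate of non-use, so the size of any distortion in the question 1 tables or the question 3 coefficients cannot be stated. The stronger readings, that content goes wholly unmeasured or that non-users are counted as faithful, are not supported. The matter concerns a descriptive and explanatory survey, not a trial's primary result. It should be fixed, and the Trial status section places the work in the planning phase, when the form can still be changed.

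**What to change.** In the shared Table 2 frame, for each component:

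1. Add a first row asking whether the component was used at all (yes/no), with a skip to the next component if not.
2. Add a row on whether the content was used as described, answered Yes, Partly or No like the three existing use rows.
3. Keep adaptation as a separate item.

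In the analysis, report use among all respondents, and fidelity, adaptation and helpfulness among users. Users-only items would be missing by design for non-users in the question 3 regression. Keep non-users there as their own category, for example not used, used but not as described, and used as described, so that they are not dropped.

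The cost is two tick-box rows per component and a slightly longer form. A three-level predictor takes two coefficients, which has to fit within the plan's intention to limit the number of predictors.
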